## 2 Summary of proposed research

**Problem statement & rationale :** A combination of platinum based chemotherapy with cetuximab is the recommended palliative chemotherapy regimen in head neck cancers., though less than 1% of patients can afford the treatment in developing countries. As a significantly cheaper alternative, we have designed an oral metronomic chemotherapy (MCT) combination of methotrexate and celecoxib. In a randomized study, we showed a survival advantage along with lower side effects, better QOL and fewer hospital visits compared to single agent cisplatin. One third of failures in head and neck cancers are seen within 6 months, and such patients have median survival of less than 3 months. This MCT was studied in these patients with median expected survival of 4 months (sent for publication). Despite the impressive initial efficacy of MCT, resistance usually develops in 3-6 months. Overexpression of multidrug transporters (Abcc2, Abcc3, and Abcg2 ) may be one of the reason behind the development of resistance to methotrexate used in MCT. Of these, Abcg2 is active in head and neck cancers and over-expressed in 50-60% of patients. Erlotinib (E) an oral tyrosine kinase inhibitor can inhibit Abcg2 mediated drug efflux. In our experience erlotinib when used after failure of cisplatin or MCT results in a promising median survival of 5.06 months.(send for publication). Upfront combination of MCT with erlotinib (MCT-E) studied by the author resulted in a 6 month survival of 80%.(accepted for publication). However these results need confirmation in a large study, along with translational research to identify the mechanism of action, resistance and biomarkers for efficacy prediction.

Drugs like methotrexate have an anti-angiogenic (metronomic) action when administered at  $\frac{1}{3}$  to  $\frac{1}{10}$  of maximum tolerable dose. We had selected a dose of 15 mg/m^2 for our MCT regimen as it was  $\frac{1}{3}$ rd of the maximum tolerated dose (MTD) . Initial preclinical data suggests that there is a dose range in which this anti-angiogenic action is seen and it is unknown if a lower dose will result in better anti-angiogenic activity. As traditional dose escalation based phase I designs are inappropriate for testing this hypothesis, we have designed a study which would incorporate clinical response and a laboratory biomarker, serum circulating endothelial cells (CECs) to determine the most biologically effective metronomic dose of methotrexate. We aim to utilize CECs as a surrogate serum marker for tumor related angiogenesis for this study.

**Study design and objectives:** This would be a prospective observational single arm study conducted in 2 stages. The primary objective of the first-stage would be to identify the optimal biological effective dose (OBD) of methotrexate in combination with celecoxib ( 200 mg PO BD) and erlotinib (150 mg PO OD).

The primary objectives of the second-stage would be to estimate the median progression free survival (PFS) and overall survival (OS) with the combination of methotrexate used at the OBD with celecoxib and erlotinib.

The secondary objectives would be to evaluate the changes in the profile of serum biomarkers ( VEGF, VEGFR1-3, Tie-2, Angiopoietin -1-2, Thrombospondin 1, Vasoinhibin, Angiostatin, Endostatin ,IL-2,CECs) tissue angiogenic biomarkers (Thymidine phosphorylase, HIF- I-alpha,

DLL, SPARC) and tissue tumor immunity related biomarkers (Foxp3 +ve T reg cells) during the course of MCT. To study the PK/PD of low dose methotrexate.

The tertiary objective would be to study gene expression changes in the tumor tissue during MCT to identify responders and mechanisms of resistance.

**Study procedures (clinical):** The study population would include patients with chemoresistant oral cancers, fit for MCT-E. In stage 1, a dose de escalation design with continuous reassessment model would be used to identify OBD of methotrexate. The disease control rate at 2 months and the proportional decline in CECs would be used for decision making regarding de escalation. Around 20-30 patients would be required for stage 1. In the second stage the combination of MCT-E would be administered in 76 patients. These patients would be followed at 8th day then subsequently every 30th day till death.

Disease progression would be defined as per RECIST criteria version 1.1. Serum and tissue biopsy would be collected in all patients at baseline prior to the start of MCT-E, at day 8 and at progression. In addition serum samples will be collected at monthly intervals till progression for serial assays of serum biomarkers.

**Study procedures (laboratory):** CECs would be measured in serum by flow cytometry. The other serum angiogenesis related markers would be quantified by ELISA. The tissue tumor immunity and angiogenesis markers would be measured by immunohistochemistry. Microarray would be used to profile the gene expression profile in the tumor specimens. PK/PD would be studied by plasma methotrexate drug level analysis.

### 3 Concept sheet

|                                |                                                                                                                                                                                                                                                                                                                                                                                                                                                     |
|--------------------------------|-----------------------------------------------------------------------------------------------------------------------------------------------------------------------------------------------------------------------------------------------------------------------------------------------------------------------------------------------------------------------------------------------------------------------------------------------------|
| Primary Registry               | Clinical Trial Registry of India (CTRI)                                                                                                                                                                                                                                                                                                                                                                                                             |
| Contact for Scientific Queries | [name] [name], DM, Department of Medical Oncology, Tata Memorial Centre
Email: [contact]                                                                                                                                                                                                                                                                                                                                             |
| Public Title                   | Study to find the recommended metronomic dose of oral methotrexate in palliative chemotherapy and its effect in oral cavity cancers                                                                                                                                                                                                                                                                                                                 |
| Scientific Title               | “Stage I/II study of oral metronomic methotrexate with celecoxib and erlotinib as palliative chemotherapy in oral cancer patients”                                                                                                                                                                                                                                                                                                           |
| Countries of Recruitment       | India                                                                                                                                                                                                                                                                                                                                                                                                                                               |
| Health Condition Studied       | Squamous cell cancers of head and neck region warranting palliative chemotherapy                                                                                                                                                                                                                                                                                                                                                                    |
| Interventions                  | Weekly oral chemotherapy with:
De escalating dose of oral methotrexate given weekly D1 
 
1. Dose Level 0: 15 mg/m^2
 
2. Dose Level I: 12 mg/m^2
 
3. Dose Level II: 09 mg/m^2
 
4. Dose Level III: 06 mg/m^2
 
5. Dose Level IV: 03 mg/m^2
 
 Fixed dose of erlotinib 150 mg OD
Fixed dose of celecoxib 200 mg BD |
| Aim                            | Stage 1 : To identify the optimal biological effective dose (OBD) of methotrexate in combination with celecoxib ( 200 mg PO BD) and erlotinib (150 mg PO OD)

Stage 2 : To estimate the median PFS in head and neck cancer patients warranting palliative chemotherapy with the combination of celecoxib 200 mg BD, erlotinib 150 mg OD and oral weekly methotrexate                                                                          |
| Objectives                     | Primary (Stage 1) 
 
1. To find out the optimal biological and clinically effective metronomic dose of weekly oral methotrexate when given in combination with celecoxib (
 
                                                                                                                                                                                                                           |

|            |                                                                                                                                                                                                                                                                                                                                                                                                                                                                                                                                                                                                                                                                                                                                                                                                                                                                                                                                                                                                                                                                                                                                                                                                                                                                                                                                                                                                                                                                                         |
|------------|-----------------------------------------------------------------------------------------------------------------------------------------------------------------------------------------------------------------------------------------------------------------------------------------------------------------------------------------------------------------------------------------------------------------------------------------------------------------------------------------------------------------------------------------------------------------------------------------------------------------------------------------------------------------------------------------------------------------------------------------------------------------------------------------------------------------------------------------------------------------------------------------------------------------------------------------------------------------------------------------------------------------------------------------------------------------------------------------------------------------------------------------------------------------------------------------------------------------------------------------------------------------------------------------------------------------------------------------------------------------------------------------------------------------------------------------------------------------------------------------|
|            | 
200 mg BID PO Daily) and erlotinib (150 mg OD daily)
 
Primary ( Stage 2) :
 
 
To find out the median PFS in Head and neck cancer patients warranting palliative chemotherapy with the combination of celecoxib 200 mg BD, erlotinib 150 mg OD and oral weekly methotrexate in biologically optimal doses
 
 
Secondary ( both stages):
 
 
Frequency of maximum grade of toxicity ( hematological and non hematological) in accordance with CTCAE version 4.03 with the combination metronomic therapy
 
Pattern of change in biomarkers according to disease control 
 
Serum angiogenic biomarkers : VEGF, VEGFR1, VEGFR2, VEGFR3, Tie-2, Angiopoietin -1, Angiopoietin -2, Thrombospondin 1, Vasoinhibin, angiostatin, endostatin ,IL-2, CECs and Endothelial progenitor cells
 
Tumor tissue angiogenic marker : Thymidine phosphorylase, Hypoxia inducible factor I-alpha, DLL, SPARC
 
Tissue tumor immunity related biomarkers :Foxp3 +ve T reg cells
 
 
 
To develop Pharmacokinetics-Pharmacodynamics (PK-PD) Model of methotrexate using CECs and serum biomarkers as PD endpoints
 
 
Tertiary (both stages)
 
 
To study gene expression changes in the tumor tissue during MCT to identify responders and mechanisms of resistance.
 
 |
| Population | 
Inclusion Criteria
 
 
Histologically proven squamous cell cancers of oral cavity with at least one measurable lesion.
 
Age > 18 years
 
ECOG PS 0 - 2
 
No uncontrolled comorbidities
 
Not affording cetuximab based chemotherapy
 
 
Exclusion Criteria
 
 
Progression free survival or disease free interval less than 6 months
 
Primary sites of malignancy in major salivary gland or nasopharynx or skin would be excluded
 
Patients receiving methotrexate for other indications will be excluded
 
Patients who had received long term Cox-2 inhibitors ( more than 3 month continuous usage) will be excluded
 
Patients with Grade 3 and above CTCAE version 4.03 QTc interval prolongation will be excluded
 
Patients who are pregnant, who are HIV positive and those with psychiatric
 
                                                                                                                                                                                                                                                                                                                                                                                                                                                                                                        |

|                          |                                                                                                                                                                                                                                                                                                                                                                                                                                                                                                                                                                                                                                                        |
|--------------------------|--------------------------------------------------------------------------------------------------------------------------------------------------------------------------------------------------------------------------------------------------------------------------------------------------------------------------------------------------------------------------------------------------------------------------------------------------------------------------------------------------------------------------------------------------------------------------------------------------------------------------------------------------------|
|                          | illness will be excluded                                                                                                                                                                                                                                                                                                                                                                                                                                                                                                                                                                                                                               |
| Study Type               | Nonrandomized open label dose de escalation study followed by single arm open label nonrandomized observational study                                                                                                                                                                                                                                                                                                                                                                                                                                                                                                                                  |
| Study procedure          | 
Intervention : Patients would receive the intended oral therapy
These patients would be monitored for response and toxicity (CTCAE version 4.02) at D8 and D30. Following which they would be assessed every month.
 
Biomarker : All patients would undergo serum biomarker investigations at least 1 day before administration of oral therapy, then at at D8, D30 and for next 3 months
 
Biopsy : Done at baseline, then at at D8 and at progression.
 
Response (Radiology) : Done at baseline and then at 1 monthly intervals
                                                              |
| Sample Size              | Around 20-30 patients would be required for stage 1. In the second stage the combination of MCT-E would be administered in 76 patients.                                                                                                                                                                                                                                                                                                                                                                                                                                                                                                                |
| Date of first enrollment | Post IRB/IEC and grants approval.                                                                                                                                                                                                                                                                                                                                                                                                                                                                                                                                                                                                                      |
| Feasibility              | We expect to complete accrual for the stage 1 study assuming the maximum number of patients within 24 months. For stage 2 study with maximum accrual in another 24 months.                                                                                                                                                                                                                                                                                                                                                                                                                                                                             |
| Significance             | 
 
1. This would be the first study to systematically determine the optimal biologically and clinically effective metronomic dose of methotrexate
 
2. Evolution in serum and tissue biomarker levels during metronomic chemotherapy and their relationship to disease control would be identified
 
3. Gene expression markers predicting for response would be identified
 
4. Gene expression changes at progression would be identified
 
5. If MCT-E improves median PFS > 3 months then a potential new option would be created in platinum resistant oral cancers
 
 |
| Funding                  | Intramural and Extramural funding to be sought                                                                                                                                                                                                                                                                                                                                                                                                                                                                                                                                                                                                         |
| Risks                    | Risks associated with the protocol include usual side effects of erlotinib (anorexia, fatigue, diarrhea and rash), celecoxib (gastritis) and low dose methotrexate ( oral mucositis)                                                                                                                                                                                                                                                                                                                                                                                                                                                                   |

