## 6 Hypothesis

**Stage 1: Whether a lower dose of methotrexate is clinically and biologically more effective than 15 mg /m^2 weekly dose?** *The dose of methotrexate associated with maximum CBR at 2 months and/or decline in CEC at D7 of first cycle would be selected .*

**Stage 2 : Whether MCT-E combination of celecoxib, erlotinib and methotrexate (in OBD) would lead to a median PFS of > 3 months in platinum insensitive oral cancers?**

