## 10 Eligibility Criteria

### 10.1 Inclusion Criteria

1. Participants must have histologically confirmed squamous cell cancers of the oral cavity warranting palliative chemotherapy.
2. Patients should have failed within 1 month of surgery/ radiation or within 6 months of platinum based systemic therapy who couldn't afford cetuximab we offer metronomic chemotherapy at present.
3. Participants must have measurable disease, defined as at least one lesion that can be accurately measured in at least one dimension (longest diameter to be recorded for non-nodal lesions and short axis for nodal lesions) as  $\geq 20$  mm with conventional techniques or as  $\geq 10$  mm with spiral CT scan, MRI, or calipers by clinical exam.

4. Age : Any age above 18 years. No maximum age.
5. ECOG performance status  $\leq 2$
6. Life expectancy of less than 6 months with standard palliative treatments.
7. Participants must have normal organ and marrow function as defined below:
  - a. Leukocytes  $\geq 3,000/\text{mcl}$
  - b. Platelets  $\geq 100,000/\text{mcl}$
  - c. Total bilirubin  $< 1.5 \times$  institutional upper limit of normal
  - d. AST(SGOT)/ALT(SGPT)  $\leq 2.5 \times$  institutional upper limit of normal
  - e. Calculated Creatinine clearance  $> 30 \text{ ml/min}$
8. The effects of erlotinib , oral methotrexate and celecoxib on the developing human fetus are unknown. For this reason and because all these agents used in this trial are known to be independently teratogenic, women of childbearing potential and men must agree to use adequate contraception (hormonal or barrier method of birth control; abstinence) prior to study entry and for the duration of study participation. Should a woman become pregnant or suspect she is pregnant while she or her partner is participating in this study, she should inform her treating physician immediately. Men treated or enrolled on this protocol must also agree to use adequate contraception prior to the study, for the duration of study participation, and 6 months after completion of protocol.
9. Both men and women of all races and ethnic groups are eligible for this trial.
10. Ability to understand and the willingness to sign a written informed consent document

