## 10.2 Exclusion Criteria

1. Participants who are receiving any other investigational agents.
2. Patients with history of aspiration pneumonia or who are unable to swallow tablets
3. Primary sites of malignancy in major salivary gland or nasopharynx or skin
4. Patients receiving methotrexate for other indications not limited to rheumatoid arthritis
5. Patients who had received long term Cox-2 inhibitors ( more than 3 month continuous usage) will be excluded
6. Patients with hypercalcemia at presentation (defined as a corrected serum calcium of  $> 10.5 \text{ mg/dL}$ ).

7. Patients with QTc prolongation defined as QTc interval greater than 440 ms in males and 480 ms in females in view of risk of sudden cardiac death associated with use of celecoxib.
8. History of allergic reactions attributed to compounds of similar chemical or biologic composition to any agents used in study.
9. Uncontrolled intercurrent illness including, but not limited to, hypertension, tuberculosis, diabetes, ongoing or active infection, symptomatic congestive heart failure, unstable angina pectoris, cardiac arrhythmia, renal failure (on dialysis), active gastrointestinal bleeding, cerebrovascular accidents, inflammatory bowel disease, known hyperkalemia (CTCAE version 4.02 grade 3 or above which is persistent over 1 week) or psychiatric illness/social situations that would limit compliance with study requirements.
10. Pregnant women and breastfeeding women are excluded from this study because celecoxib / erlotinib and methotrexate are agents with the potential for teratogenic or abortifacient effects. Because there is an unknown but potential risk for adverse events in nursing infants. These potential risks may also apply to other agents used in this study.
11. HIV-positive, Hepatitis B and C seropositive patients are excluded from this study.
12. Patients with previous history of other cancers.

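### The concept sheet excludes the early-failure patients whom Section 10.1 requires, and the protocol does not say which eligibility list governs

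*Protocol*

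**What the plan says.** **Interval criterion.** The concept sheet (Section 3, Population) gives as its first exclusion "Progression free survival or disease free interval less than 6 months". Its inclusion list has no early-failure requirement. Section 10.1 item 2 states the reverse: "Patients should have failed within 1 month of surgery/ radiation or within 6 months of platinum based systemic therapy". Section 10.2 does not carry the 6-month exclusion.

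**Population elsewhere.**
- Section 2: "The study population would include patients with chemoresistant oral cancers, fit for MCT-E".
- Section 6 asks whether the combination "would lead to a median PFS of > 3 months in platinum insensitive oral cancers".
- Section 10.1 item 6 requires "Life expectancy of less than 6 months with standard palliative treatments".
- The concept sheet's own Significance row refers to platinum-resistant oral cancer.
- The concept sheet's Stage 2 objective reads "To find out the median PFS in Head and neck cancer patients warranting palliative chemotherapy", and its Stage 2 aim is worded in the same way.
- Section 7.1 speaks of recurrent oral cancer.

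**QTc.** The concept sheet says "Patients with Grade 3 and above CTCAE version 4.03 QTc interval prolongation will be excluded". Section 10.2 item 7 excludes a "QTc interval greater than 440 ms in males and 480 ms in females".

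**The concern.** An interval under 6 months is a reason to exclude in one list and, in substance, a condition of entry in the other. Both lists are part of the protocol, and nothing in it gives either one precedence. Section 17 says that eligibility is documented on a separate checklist. That checklist is an appendix not available here, so it cannot be seen which list it follows.

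The stakes come from the design. Stage 2 has one arm and is judged against a fixed 3-month PFS of 0.50 (Section 15). With no concurrent control, a shift towards patients with a better outlook could not be told apart from a treatment effect. Stage 1 selects its dose on two endpoints, one of which is clinical benefit at 2 months. That endpoint depends on prognosis, so a different case mix could change the dose carried into Stage 2.

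**Working it through.** This is a comparison of texts, and the plan has no figure of its own to reproduce. The arithmetic only sizes the consequence.

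**Step 1: overlap of the two lists.**
- *Surgery or radiation branch.* Failure no later than 1 month afterwards means an interval of at most 1 month. Since 1 < 6, the concept sheet excludes every such patient.
- *Platinum branch, interval counted from the end of platinum.* Failure within 6 months means an interval under 6 months, so these patients are also excluded.
- *Platinum branch, PFS counted from the start of platinum.* The concept sheet does not define the start. As an assumed example, take a patient never free of disease who had 4 months of platinum and progressed 3 months after the last dose. PFS is 4 + 3 = 7 months, so the concept sheet does not exclude this patient. The gap from the last dose is 3 months, so Section 10.1 is met.

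The overlap is therefore empty in the first branch. In the second it is narrow and depends on the undefined start. Essentially no patient satisfies both lists.

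**Step 2: outlook of the two populations.** Inputs are from Section 4.2, both on metronomic methotrexate and celecoxib.

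| Cohort | Median OS | 95% CI |
|---|---|---|
| Randomised study: chemonaive, or failure-free at least 3 months | 249 days | 222.5 to 275.5 |
| Retrospective series: early failures in oral cancer | 110 days | 85 to 134 |

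The ratio of medians is 249 / 110 = 2.26, and the intervals do not overlap. The cohorts come from different studies, and the first used a 3-month cut, not 6 months. The comparison shows that time to failure goes with a large difference in outlook. It does not estimate survival in the patients whom the concept sheet would admit.

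**Step 3: what the PFS figure can carry.** Section 4.2 gives a median PFS of 101 days (95% CI 58.2 to 143.7) for the metronomic arm of the randomised study, without erlotinib. Under the exponential model of Section 15, with 3 months taken as 91.3 days:

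S(3 months) = 0.5^(91.3 / median)

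- Point estimate: 0.5^(91.3 / 101) = 0.534
- Lower limit: 0.5^(91.3 / 58.2) = 0.34
- Upper limit: 0.5^(91.3 / 143.7) = 0.64

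If the true rate were 0.534, a one-sided 5% normal test against 0.50 with 63 patients would reject when the observed rate exceeds 0.50 + 1.645 × 0.5 / √63 = 0.604. The standard error is √(0.534 × 0.466 / 63) = 0.063. The chance of rejection is 1 − Φ((0.604 − 0.534) / 0.063), about 13.5% before rounding, against a nominal 5%. This is illustrative only, because the range 0.34 to 0.64 lies on both sides of 0.50.

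**The case against.** The strongest defence is that the concept sheet is a registry-style synopsis and that Section 10 holds the full criteria. Almost everything else points to early failures: Section 2, the unmet need in Section 4.2, Section 6, the biopsy rationale in Section 12.2, the life-expectancy criterion, the recruitment pool of chemoresistant patients in Section 25, and the concept sheet's own Significance row. A careful reader would take the stray line for a drafting slip. That stands, and it shows which text needs correcting. It does not remove the contradiction, because no rule makes Section 10 govern.

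Some stronger readings are tempting, and the documents do not support them:
- *That no patient at all could fit both lists.* This depends on where the interval starts. If it runs from the start of platinum, a few could.
- *That the wrong population is being enrolled.* The checklist is not available, and the concept sheet puts first enrolment after ethics and grant approvals. Wrong enrolment is a risk only.
- *That later failures already beat the null without erlotinib.* The 101-day median is compatible with a 3-month PFS on either side of 0.50. It should also not be set against the 110-day figure, which is overall survival.
- *That the 0.50 null is stated for platinum-insensitive disease.* Section 15 attributes it to a standard cancer therapy and names no population. The link comes from Section 6.
- *That the head and neck wording admits other primary sites.* The concept sheet's first inclusion criterion restricts entry to the oral cavity.

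On QTc, the two rules are not mutually exclusive, and the protocol gives no millisecond value for the CTCAE grade. The size of that gap cannot be established here, and it adds nothing to the weight of the main point.

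**Conclusion.** The contradiction between the concept sheet and Section 10.1 item 2 is real and unresolved. As written, the two lists jointly leave essentially no eligible patient. This conclusion needs no numerical assumption beyond the reading of the interval start set out above.

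If the concept sheet were applied alone, the trial would take later failures. The best available evidence that this matters is the 249-day against 110-day contrast in median overall survival, a ratio of about 2.3, from different cohorts and with a 3-month cut. A shift of that kind would undermine both the single-arm comparison with a 3-month PFS of 0.50 and the Stage 1 dose selection. The 0.534 and 13.5% figures are illustrations, not estimates of bias.

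The protocol's other statements indicate that the concept-sheet line is the faulty one. The correction should be made because an eligibility rule is wrong as written and costs almost nothing to repair. The QTc difference is a separate inconsistency. The Stage 2 population labels are loose wording.

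**What to change.** 1. Remove the 6-month exclusion from the concept sheet, or otherwise reconcile it with Section 10.1 item 2, so that one early-failure criterion appears in the concept sheet, Section 10 and the eligibility checklist.
2. In that criterion, define the date from which each interval runs, for the surgery or radiation branch and for the platinum branch. Clean the sentence as well: item 2 as printed runs on into a fragment on cetuximab affordability and current practice that appears to come from Section 4.2.
3. Use one description of the Stage 2 population in the concept sheet's aim and objective, Section 6 and Section 7.1.
4. Separately, reconcile the two QTc exclusions to a single rule and carry it into the checklist. Which rule is appropriate is a clinical decision for the sponsor.
5. If any patients were enrolled before the correction, check them against the reconciled list.

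The cost is a text amendment and a revised checklist. Section 23.2 already requires formal amendment and ethics review for changes to the patient population. This point calls for no change to the sample size or the analysis.
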